### Strategies to improve adherence to interventions {11c}

Our study team will devise and implement regular communication strategies to enhance the adherence of participants to the research interventions. This strategy will involve weekly communication with participants via WeChat and telephone, which will not only help increase their engagement and enthusiasm for the study, but also will allow us to stay informed about their psychological well-being. Through these communication channels, the research team will closely monitor and identify any potential side effects or adverse events experienced by participants, thereby ensuring the safety and efficacy of the study.

### Relevant concomitant care permitted or prohibited during the trial {11d}

Throughout the study, foundational treatment will be emphasized for patients with diabetes. Participants are permitted to continue their pre-existing, stable (≥4 weeks of use prior to enrollment) conventional glucose-lowering medications—including metformin, sulfonylureas, sodium-glucose cotransporter-2 inhibitors, insulin and its analogues—in addition to the investigational product (liraglutide or placebo), in order to comply with ethical standards and maintain glycemic stability, while the initiation or switch to dipeptidyl peptidase-4 inhibitors, other GLP-1 receptor agonists, and related preparations is strictly prohibited. To ensure comparability of background therapy between groups, we will implement stratified randomization based on baseline insulin use and will meticulously record and compare all baseline glucose-lowering medications across groups prior to analysis to confirm randomization balance.

For the basic treatment protocol, the study will adhere to the recommendations outlined in the Chinese Diabetes Prevention and Treatment Guidelines (2020 edition).

### Provisions for post-trial care {30}

After the trial concludes, the participants will undergo regular mental health screenings to monitor for any long-term side effects related to depression.

### Outcomes {12}

Observational indicators include two types: efficacy and safety indicators.

### Efficacy indicators

#### Primary outcome measures

1) Efficacy indicators include fasting plasma glucose, 2-hour postprandial glucose, body mass index (BMI), glycated hemoglobin (HbA1c), and lipid profiles (total cholesterol, triglycerides, low-density lipoprotein cholesterol, and high-density lipoprotein cholesterol).2) Depression scale scores, derived from the Hamilton Depression Scale (HAMD), will be used to assess the severity of depressive symptoms. This validated clinical tool provides quantifiable measurements of both condition severity and treatment response in depression management (27).3) Resting-state functional magnetic resonance imaging parameters comprise three key metrics: the amplitude of low-frequency fluctuations (ALFF), regional homogeneity (ReHo), and functional connectivity (FC). These biomarkers quantitatively reflect spontaneous neural activity patterns and dynamic connectivity alterations across brain networks. They are widely employed in neuropsychiatric research, particularly in depression studies (28).

### MRI acquisition protocol

Neuroimaging data will be acquired using a Siemens 3T Trio MRI system (Erlangen, Germany) equipped with an 8-channel phased-array head coil. Prior to scanning, the participants will receive standardized instructions to maintain their eyes closed, relax without focused thinking, and minimize head motion during acquisition. For obtaining sagittal T1-weighted imaging structural images, a three-dimensional magnetization-prepared rapid gradient echo sequence will be employed, with the following specific parameters: TR 1900 ms, TE 2.52 ms, TI 900 ms, a flip angle of 9°, 160 slices, a voxel size of 1 mm × 1 mm × 1 mm, a field of view of 250 mm × 250 mm, and a matrix resolution of 256 × 256. Resting-state brain functional images will be acquired using a planar gradient echo sequence with the following specific parameters: TR 2000 ms, echo time 30 ms, flip angle 90°, 33 slices, slice thickness 4 mm. field of view 240 mm × 240 mm, matrix 64 × 64, and total acquisition 200 time points. Furthermore, conventional T2-weighted imaging and fluid-attenuated inversion recovery sequences will be used to exclude potential white matter degeneration or lacunar infarct foci.

### Preprocessing and index calculation of rs-fMRI data

All preprocessing will be performed using the DPABI v6.0 toolbox in MATLAB software (29). To achieve data balance, the first 10 time points of each participant’s data will be excluded. Subsequently, the following preprocessing steps will be implemented: (1) temporal layer correction; (2) head motion correction, with exclusion of data if the participant’s head translation exceeds 2 mm or rotation exceeds 2°; (3) covariate regression (including Friston 24 head motion parameters, global brain signal, white matter signal, and cerebrospinal fluid signal); (4) spatial normalization (resampling voxel size to 3 mm × 3 mm × 3 mm); (5) spatial smoothing (Gaussian kernel full width at half maximum of 6 mm); (6) removal of linear drift; and (7) band-pass filtering (bandwidth of 0.01–0.10 Hz).

Resting-state brain functional indices will be derived using DPABI v6.0. The amplitude of low-frequency fluctuations will be computed after the aforementioned preprocessing stages, focusing on ALFF values within the frequency range of 0.01–0.08 Hz. The regional homogeneity values reflect Kendall’s coefficient of concordance, encompassing a voxel and its 26 neighboring voxels. Spatial smoothing will not be applied during preprocessing; however, Gaussian smoothing will be conducted after computation using a smoothing kernel diameter of 6 mm.

Given the asymmetry of the human brain, a symmetric template in the standard space will be constructed from the T1-weighted structural images of all participants. This template will subsequently be utilized to re-standardize the functional images. Following spatial smoothing, removal of linear drift, and filtering, the Pearson correlation coefficient between symmetric voxels across both cerebral hemispheres will be calculated as the mean volume homogeneity correlation value. These indices will undergo Fisher-z transformation to generate z-values, which will then be used for further statistical analysis.

### Secondary indicators

Secondary indicators include changes in inflammatory factors [tumor necrosis factor-α (TNF-α), interleukin-6 (IL-6)]; oxidative stress markers [superoxide dismutase (SOD), malondialdehyde (MDA)]; homeostatic model assessment of insulin resistance; insulin sensitivity index; and homeostatic model assessment of β-cell function.

### Safety indicators

Safety indicators include adverse drug reactions, hypoglycemic reactions, vital signs, electrocardiograms, and hematological and biochemical indicators, including routine blood tests and liver and kidney functions. During follow-up, close monitoring of changes in the patients’ mood and vigilance regarding the risk of suicide is essential.

### Participant timeline {13}

Outcome assessments will be performed at baseline, followed by three subsequent visits. At baseline assessment, we will gather data on patient demographics, including age, gender, educational level, employment status, marital status, and comorbidities. Additionally, we will document the date of initial diagnosis, symptom duration, and details of prior medications and treatment regimens. The participants are required to revisit the hospital at 4, 8, and 12 weeks after medication initiation for a series of evaluations. These include height and weight measurements, completion of pertinent laboratory tests, and the administration of depression and cognitive function scales. These assessments aim to provide a comprehensive evaluation of treatment efficacy. The detailed enrollment process and comprehensive schedule of the evaluation results are presented in **Table 3**.

**Table 3 T3:** Schedule of outcome measures and trial-related activities.

Items	Enrollment day	4 weeks	8weeks	12 weeks
Inclusion screening				
Sign informed consent	*√*			
Record general information	*√*			
Gender	*√*			
Age	*√*			
Body weight	*√*	*√*	*√*	*√*
height	*√*	*√*	*√*	*√*
Waist circumference	*√*	*√*	*√*	*√*
Hip circumference	*√*	*√*	*√*	*√*
Medical history and treatment history	*√*			
Combined disease and medication records	*√*			
life history	*√*			
Safety				
blood routine examination	*√*			*√*
routine urine test	*√*			*√*
stool routine examination	*√*			*√*
liver function	*√*			*√*
renal function	*√*			*√*
Electrocardiograph	*√*			*√*
Adverse events and complications		*√*	*√*	*√*
Efficacy index				
Hamilton Depression Scale 24 scores	*√*			*√*
Blood glucose (fasting and 2 hours after meals)	*√*			*√*
glycosylated hemoglobin	*√*			*√*
blood lipids	*√*			*√*
tumor necrosis factor-α, Interleukin-6	*√*			*√*
super Oxide Dismutase,malondialdehyde	*√*			*√*
HOMA Insulin resistance Index	*√*			*√*
Insulin sensitivity Index	*√*			*√*
HOMA Islet beta Cell Function Index	*√*			*√*
resting-state functional magnetic resonance imaging	*√*			*√*

### Sample size {14}

Determining the appropriate sample size is critical when devising a clinical trial, including a pilot study. These preliminary trials are designed to assess the feasibility and address pragmatic considerations for subsequent full-scale trials. Consequently, the sample size for these pilot studies is calibrated to provide estimates of study parameters with an acceptable level of precision rather than being predicated on traditional hypothesis testing (30). Sim et al. recommended a minimum of 50 participants (25 per group) to achieve the pilot trial feasibility goal (31). In previous clinical studies on mental disorders, 10% of the liraglutide group and 2% of the placebo group withdrew from the trial after 16 weeks (32). However, in a study of liraglutide in overweight/obese patients with type 2 diabetes, only two patients in the liraglutide group (198 cases) and four patients in the placebo group (198 cases) withdrew from the trial after 56 weeks (33). Based on data from other pilot trials of liraglutide (34), we assumed that the conservative dropout rate at 3 months would be between 10% and 15%; therefore, we would need to recruit approximately 60 participants (every 30) to provide a reliable estimate.

### Recruitment {15}

Eligible participants will be identified by reviewing the outpatient and inpatient records from the endocrinology department. For patients who fulfill the inclusion criteria, an invitation to participate and the trial information will be sent to their email address. Following the receipt of the written invitation, we will make a telephone call within one to two weeks to ascertain their interest in the study. Patients who desire to participate will be provided with a comprehensive study protocol and an outline of the process to enhance their understanding of the trial scope and procedures.

### Assignment of interventions: allocation

#### Sequence generation {16a}

After obtaining informed consent and post-baseline assessments, researchers will be alerted to initiate the group allocation process. Participants will be randomly assigned to one of the two groups at a 1:1 ratio using a system of generated random numbers. These numbers will be stored in opaque sealed envelopes, from which each participant will randomly selected one, thereby determining their allocation to either the treatment or control group. Patients will be evenly distributed between two interventions: once-daily administration of placebo in a blinded manner and once-daily liraglutide in a blinded manner. The hospital’s central pharmacy will be responsible for dispensing both placebo and the active drug. To maintain the integrity of the double-blind protocol, participants, researchers, and study monitors will not be privy to treatment assignments within the placebo and liraglutide groups at any time.

#### Concealment mechanism {16b}

Liraglutide and its placebo will be manufactured to be identical in appearance to ensure that the participants are blinded to the assigned medication. Sealed envelopes, each corresponding to a participant and containing details of the randomization sequence, will be stored securely to ensure that they are not accessible to the researchers at any time, thus preserving the integrity of the double-blind study design.

#### Implementation {16c}

The randomization procedure will be implemented using a web-based randomization system provided by the Chinese Clinical Trial Registry (http://www.medresman.org.cn/login.aspx).

### Assignment of interventions: blinding

#### Who will be blinded {17a}

A triple-blind design will be rigorously maintained throughout the trial period, encompassing all participants, healthcare personnel, and investigative staff from initial enrollment through the terminal follow-up assessment. Systematic disclosure of treatment allocations shall be deferred until study completion for all enrollees and conclusive verification of analytical results has been achieved.

#### Procedure for unblinding if needed {17b}

In accordance with the clinical research protocols, trial participants are required to immediately notify the principal investigator or research team upon experiencing adverse events. For serious adverse events, the principal investigator must conduct a causality assessment immediately after notification to evaluate the potential association with the investigational product. When deemed medically necessary, emergency unblinding procedures may be initiated by the investigator by accessing the confidential randomization code system maintained by the clinical trial pharmacy.

### Data collection and management

#### Plans for assessment and collection of outcomes {18a}

All the study-related data of the enrolled patients will be securely recorded using an electronic storage system. Patient data will be entered into an Excel database to ensure accuracy and confidentiality will be strictly maintained, with no disclosure of this information to researchers outside the study team until the conclusion of the study. Inspectors will conduct regular audits to review and correct entries, thereby ensuring the highest standards of data quality. Before the study begins, uniform standard operating procedures will be developed and comprehensive training will be delivered to the research staff, physicians, and nursing personnel at each participating center.

#### Plans to promote participant retention and complete follow-up {18b}

During the preliminary phase of the investigation, implementing weekly telephone follow-ups with individual participants will be used to increase retention rates. This structured engagement strategy serves a dual purpose: it enables investigators to obtain timely feedback regarding participants’ needs, while simultaneously fostering increased study commitment and mutual trust. The research protocol includes establishing multiple communication channels (e.g., phone, WeChat, email) with explicit instructions for emergency contact and ongoing support availability. These protocol enhancements are designed to ensure sustained participant comfort throughout the research lifecycle, thereby optimizing both intervention efficacy and overall satisfaction metrics.

### Data management {19}

Experienced research assistants will manage the collection and documentation of clinical data. Clinical examination results will be carefully documented in case report forms and entered into an electronic format. To ensure data entry accuracy, a dedicated technician will conduct consistency verification. All collected information will be stored securely in a password-protected digital system to maintain confidentiality. The study must comply with Good Clinical Practice guidelines, which emphasize safeguarding participants’ rights and well-being while ensuring data integrity and traceability for source verification. Participants retain the right to withdraw from the study at any time without justification, and this choice will not impact their future medical treatment or legal entitlements. After the completion of the study, participant records will be maintained for 3 years to enable future review and analysis.

### Confidentiality {27}

All personally identifiable records will be securely stored in a separate study database, and sharing will be strictly confined to the research context. Access to intervention-related data will be granted exclusively to authorized healthcare practitioners and principal investigators involved in the study.

#### Plans for collection, laboratory evaluation, and storage of biological specimens for genetic or molecular analysis in this trial/future use {33}

Upon blood collection, the specimens will undergo centrifugation and be promptly preserved at -80°C in laboratory freezers at the Chengdu Shuangliu District Traditional Chinese Medicine Hospital. All trial-related samples will be labeled with unique patient identification codes to maintain anonymity by excluding personally identifiable information. The participants retain the option of authorizing biological sample retention for potential future investigations. Following the conclusion of the study, de-identified specimens will be maintained in cryogenic storage for a 3-year period, after which they will be systematically incinerated in compliance with regional regulatory standards. No genomic profiling is currently intended for these biological materials.

### Statistical methods

#### Statistical methods for primary and secondary outcomes {20a}

The aim of this study is to compare the effectiveness of the two treatment regimens by assessing participants twice, once at baseline and again at the 3-month follow-up. To control for potential confounding variables, we will statistically adjust for participants’ age, gender, body mass index, and Hamilton Depression Rating Scale scores in accordance with the STRIVE criteria. Numbers and percentages will be used to express categorical variables and median and interquartile range will be used for continuous variables. Primary outcome measures (e.g., HAMD score, HbA1c, body weight) will be analyzed using Linear Mixed-Effects Models. The models will include treatment group, time, and the group-by-time interaction as fixed effects to test for between-group differences in treatment effect and its change over time. Subject-specific intercepts will be included as random effects. Analyses will be adjusted for pre-specified confounding variables, including age, sex, baseline BMI, and baseline HAMD score, which will be entered into the models as fixed-effect covariates. For missing data due to dropout, Multiple Imputation will be employed. Secondary outcomes and baseline characteristics will be described and compared as originally planned. All analyses will be performed using SPSS v.22.0 (SPSS Inc., Chicago, IL, USA) and the lme4 package in R. A p-value < 0.05 will be considered statistically significant, whereas a p-value <0.01 will be regarded as indicating a high degree of statistical significance.

The DPABI v6.0 toolkit will be used to perform two-sample t-tests on the whole-brain ALFF, ReHo, and VMHC maps of the two groups of participants. To correct for multiple comparisons across voxels, the statistical significance of the resulting maps will be assessed using Gaussian Random Field (GRF) theory, a method for family-wise error (FWE) rate correction. The threshold was set at a voxel-level significance of P < 0.001 and a cluster-level significance of P < 0.05.

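### The mixed model offers two between-group tests without saying which gives the treatment effect; for outcomes measured only at baseline and week 12, such as HbA1c, the group term is not a treatment test

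*Protocol article*

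**What the plan says.** Section {20a} says the treatments will be compared by "assessing participants twice, once at baseline and again at the 3-month follow-up". Primary outcomes, with HAMD, HbA1c and body weight as examples, go into linear mixed models with "treatment group, time, and the group-by-time interaction as fixed effects to test for between-group differences in treatment effect and its change over time". The covariance part is brief: "Subject-specific intercepts will be included as random effects". The covariates are "age, sex, baseline BMI, and baseline HAMD score, which will be entered into the models as fixed-effect covariates". The decision rule is "A p-value < 0.05 will be considered statistically significant", with no split between terms. The software is "SPSS v.22.0 (SPSS Inc., Chicago, IL, USA) and the lme4 package in R". Section {20b} plans no analysis beyond {20a}.

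Table 3 (Participant timeline {13}) ticks the row "Hamilton Depression Scale 24 scores" at enrollment and week 12 only. The same holds for glucose, HbA1c and lipids. Body weight is ticked at all four visits.

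**The concern.** The sentence gives the model two between-group purposes: a difference between arms, and the change of that difference over time. These correspond to the group term and the group-by-time term, and neither is ranked as the result.

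With only baseline and week 12 available, a time term can exist only if baseline is a response. The group term then includes a value taken before any drug was given, and only the contrast at week 12 answers the trial's question. Two people reading the same fitted model could reach different conclusions. One could report no difference between the arms from the group row, and the other a significant effect from the interaction row. For a pilot meant to inform a larger trial, an estimate that is half the week-12 effect but is labelled as the group effect would also mislead planning.

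**Working it through.** **Inputs from the protocol.** Threshold 0.05 (two-sided assumed); two time points; random intercept, hence equal variances and one correlation ρ; 60 recruited, 30 per arm. The recruitment figure reproduces: 25/(1 − 0.15) = 29.4, so 30 per arm.

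**Assumptions, not in the protocol.** ρ between baseline and week 12 of 0.3 to 0.7; a week-12 effect d of 0.5 or 0.8 SD; 26 analysed per arm (30 less about 13%) unless stated otherwise.

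**1. What the group term estimates (HbA1c-type outcomes).** The arms differ by 0 in expectation at baseline and by d at week 12.
- Averaged over time: (0 + d)/2 = d/2.
- Baseline as reference level: 0, because the term is the pre-treatment difference.

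**2. False-positive rate if either term counts.**
- Averaged coding: the terms rest on the sum and the difference of two equal-variance measurements, which are uncorrelated. The rate is 1 − 0.95² = 9.75%. Simulation gives 9.6-9.9% at 30 per arm and 9.7-10.2% at 26.
- Baseline as reference: the tests correlate at −√((1 − ρ)/2), which is −0.59, −0.50 and −0.39 for ρ = 0.3, 0.5 and 0.7. The rates are 8.8%, 9.1% and 9.4%.
- One named term: simulated 4.8-5.2%.

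**3. Power (HbA1c-type, averaged group term).** The interaction uses effect d with SD √(2(1 − ρ)). The group term uses d/2 with SD √((1 + ρ)/2). At d = 0.5, ρ = 0.5 and 26 per arm:
- Interaction: 0.5 × √13 / 1 = 1.80; simulated power 42%.
- Group: 0.25 × √13 / √0.75 = 1.04; simulated power about 18%.
- The two terms give different verdicts in about 45% of simulated trials (38-59% over ρ = 0.3 to 0.7).

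The same formulas at 25 per arm (normal approximation):

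| d | ρ | Interaction | Group |
|---|---|---|---|
| 0.5 | 0.3 | 32% | 19% |
| 0.5 | 0.5 | 42% | 17% |
| 0.5 | 0.7 | 63% | 16% |
| 0.8 | 0.3 | 67% | 42% |
| 0.8 | 0.5 | 81% | 37% |
| 0.8 | 0.7 | 96% | 34% |

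**4. HAMD, with its own baseline as covariate.** Simulated at 26 per arm under no effect, the interaction alone is significant in 6.2-7.5% of trials and either term in 7.3-8.2%. The second test therefore adds about 1 percentage point. Most of the excess over 5% is already in the interaction test, because baseline HAMD is both response and covariate and the standard errors suffer. At d = 0.5 and ρ = 0.5, power is 47% (group) and 49% (interaction), with disagreement in 17% of trials. At 30 per arm and d = 0.8 it is 92% and 88%. The group estimate is still d/2, but its power is not materially lower.

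**5. Body weight, if all four visits are modelled.** The averaged term is (0 + 1/3 + 2/3 + 1)/4 = 50% of the week-12 effect with linear build-up, and (0 + 1 + 1 + 1)/4 = 75% with an immediate full effect.

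**The case against.** The strongest reply is that the protocol never says significance on either term counts as success. Many statisticians would take the interaction as the deciding test, and the choice of contrast is ordinary analysis-plan detail. The first two parts stand: the 9-10% is conditional on a rule that is not written down. The third stands only in part. Section {20a} is not silent; it states what the terms test, and for outcomes with two time points one of the two stated tests is not a test of treatment.

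Three stronger readings are tempting and are not supported.
- A reader might infer a 10% error rate and a diluted effect with lost power for every outcome. HAMD, the trial's particular focus, shows neither the doubling nor the power loss, and the exact halving does not carry over to four-visit body weight.
- A reader might infer that SPSS and R will test different hypotheses under one label. The text, "All analyses will be performed using SPSS v.22.0 (SPSS Inc., Chicago, IL, USA) and the lme4 package in R", does not say that the same model is fitted in both, and the conflict would rest on assumed default codings.
- A reader might attribute all of the HAMD excess to the second test. Most of it belongs to the separate covariate and standard-error problem.

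The stakes are also limited: the sample size is justified by precision rather than hypothesis testing, and the trial is a pilot. But {20a} still declares significance at 0.05 and 0.01.

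**Conclusion.** The point holds for outcomes with baseline and week 12 only and no own-baseline covariate: HbA1c, glucose and lipids as scheduled in Table 3. There the group term is half the week-12 effect or none of it, depending on coding. The per-outcome error would be about 9-10% if either term were accepted. At 0.5 SD, ρ = 0.5 and 26 per arm, power is about 18% for the group term against 42% for the interaction. The halving follows from the design; the power figures rest on the assumed effect size, correlation and numbers analysed.

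The halving also depends on Table 3 and the opening of {20a}. Section {11a} speaks of outcome assessment at four time points in general; if that schedule applied to these outcomes, the averaged term would be about 50-75% of the week-12 effect under the two build-up patterns considered for body weight. For HAMD the practical consequence is small. This is a wording fault with a real but bounded effect, worth correcting because the correction costs almost nothing.

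**What to change.** In {20a}, replace the two-part purpose of the model with one statement. For each outcome, the treatment effect is the between-arm contrast at week 12 with its 95% CI, taken from one named model. The group main effect will not be interpreted as a treatment test, and any week 4 and week 8 contrasts are descriptive.

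The model can be either of the following:
- the group-by-time contrast at week 12; or
- preferably, the week-12 group difference with the baseline means of the arms constrained equal.

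These are different estimators, so the text must choose one. The preference is for precision: at 25 per arm, d = 0.5 and ρ = 0.5, a baseline-adjusted week-12 comparison, the benchmark for the constrained model, has about 53% power against 42% for the interaction (normal approximation).

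The cost is one or two sentences, with no new data or patients. The downside is that a significant group term can no longer be reported as an effect. The HAMD covariate and standard-error problem is not solved by this change and needs its own correction.

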### Intervention description {11a}

#### Randomization and intervention

Upon providing written informed consent, participants will be randomly allocated in a 1:1 ratio to either the experimental or control group. The experimental group will receive active treatment with liraglutide injections, whereas the control group will receive matching placebo injections. Treatment protocols will be determined by two endocrinologists and a psychiatrist involved in screening. Both groups will receive identical standard care, including diabetes-specific dietary plans and exercise guidance throughout the 12-week study period. Outcomes will be assessed at four time points: baseline and weeks 4, 8, and 12 (dual assessment at week 12 for the interim and final evaluations).

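### Reconcile two versus four visits in section 20a; if all four weight/BMI visits are analysed, a random intercept alone makes a single week-12 or slope test anticonservative

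*Protocol article*

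**What the plan says.** On the model, section 20a states "Primary outcome measures (e.g., HAMD score, HbA1c, body weight) will be analyzed using Linear Mixed-Effects Models". It continues "The models will include treatment group, time, and the group-by-time interaction as fixed effects", and then "Subject-specific intercepts will be included as random effects". It names no random slope and no other within-patient covariance. It does not say whether time is categorical or continuous, or which interaction test counts. The significance rule is "A p-value < 0.05 will be considered statistically significant".

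On the number of visits, the article gives different answers:

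- Section 20a opens by describing the comparison as "assessing participants twice, once at baseline and again at the 3-month follow-up".
- The randomization and intervention section says "Outcomes will be assessed at four time points: baseline and weeks 4, 8, and 12".
- The participant timeline says "The participants are required to revisit the hospital at 4, 8, and 12 weeks after medication initiation for a series of evaluations".
- Table 3 ticks body weight and height at enrollment and at weeks 4, 8 and 12. BMI, a listed primary outcome, therefore has four values per patient. The row "Hamilton Depression Scale 24 scores" and the rows for glucose, HbA1c and lipids are ticked only at enrollment and week 12.

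**The concern.** A random intercept with independent residuals gives every pair of visits the same correlation. It also makes the change to week 12 no more variable than the change to week 4. With repeated weights over 12 weeks that is unlikely: patients on diet and exercise plans and differing background glucose-lowering drugs will not follow parallel paths, so the variance of change grows with time. The model then pools small early variances with the large week-12 variance, and its standard error for the week-12 difference or for the slope is too small.

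The baseline covariates (age, sex, BMI, HAMD) do not cure this, because they are constant within a patient and leave the within-patient error as it is. At stake is a confidence interval that is too narrow on one primary outcome. A weight or BMI difference might also be called significant, or highly significant at 0.01, on an understated standard error.

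**Working it through.** **Inputs from the article.** Random intercept only; group, time and their interaction; alpha 0.05 (two-sided assumed); 30 per arm; weight and height at weeks 0, 4, 8 and 12. The sample size reproduces: 50/(1 - 0.10) = 55.6, so 56, and 50/(1 - 0.15) = 58.8, so 59, against a stated total of about 60. No type I error other than the nominal 0.05 is stated, and no variance or correlation.

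**Assumed inputs.** D is the SD of patients' true 12-week weight change, 1-4 kg. e is the visit-to-visit noise SD, 0.5-1.5 kg.

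**Formula.** Take complete data, k visits and true within-patient covariance Σ. The random-intercept model estimates residual variance s² = tr(PΣ)/(k - 1), with P = I - J/k. For a contrast c summing to zero, the model uses variance s²·c'c and the truth is c'Σc. Let R = c'Σc/(s²·c'c). The actual level is 2[1 - Φ(1.96/√R)]. The number of patients cancels.

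**Two visits.** s² = Var(change)/2 and c'c = 2, so the model variance equals Var(change), which is the truth. R = 1 and there is no inflation. Simulation gave 0.049-0.052.

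**Four visits, patient-specific slopes.** Code the visits 0, 1, 2, 3; the slope variance is D²/9.

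- s² = 5D²/27 + e²
- Week 12: R = (D² + 2e²) / [2(5D²/27 + e²)]
- Slope: R = (25D²/9 + 5e²) / [5(5D²/27 + e²)]

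| D (kg) | e (kg) | R, week 12 | level | R, slope | level |
|---|---|---|---|---|---|
| 1 | 1.0 | 3/2.37 = 1.27 | 0.081 | 7.78/5.93 = 1.31 | 0.087 |
| 3 | 1.0 | 11/5.33 = 2.06 | 0.172 | 30/13.33 = 2.25 | 0.191 |
| 4 | 0.5 | 16.5/6.43 = 2.57 | 0.221 | 45.69/16.06 = 2.84 | 0.245 |
| any | 0 (limit) | 9/3.33 = 2.70 | 0.233 | 25/8.33 = 3.00 | 0.258 |

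**Weaker drift (random walk), D = 1.5, e = 1.5.** s² = (5/6)(2.25/3) + 2.25 = 2.875. For week 12, R = 6.75/5.75 = 1.17 and the level is 0.070, or 1.4 times nominal. The slope level is 0.077.

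**Serial correlation, AR(1) with 0.5-0.98 between adjacent visits.** Slope 0.113-0.168; week 12 0.092-0.142.

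**Exactly equal correlation.** R = 1; simulated 0.052 for both contrasts.

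**Joint 3-df interaction test.** Simulated 0.048-0.103 across all four-visit scenarios (8,000 null trials each).

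**Baseline as covariate only, weeks 4, 8 and 12 as outcome (patient-specific slopes).** Slope 0.087-0.153; week-12 group difference 0.122-0.154. Dropping baseline from the response does not remove the problem.

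**Checks by fitting the model.** In 300 null trials with all four planned covariates (D = 2, e = 0.7), the week-12 contrast rejected in 16% and the slope in 18%; the formulas give 0.168 and 0.187. In 150 REML fits with baseline BMI and age (D = 3, e = 1), the figures were 0.213 and 0.220. Their Monte Carlo error is about √(0.2 × 0.8/150) = 0.033, so they are compatible with 0.172 and 0.191.

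**Standard error.** √1.17 = 1.08 and √2.57 = 1.60, so the true SD of the week-12 difference is about 1.1 to 1.6 times the model's standard error.

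**The case against.** The strongest reply is that the section which specifies the model also says participants are assessed twice, and with two assessments the random-intercept model is adequate. That stands. The defect visible on the page is the unreconciled visit count, and the covariance point follows only if four visits are analysed. It does not clear the text, because two other places and the weight and height rows of Table 3 give four visits.

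A reader might infer that the HAMD analysis, the trial's main interest, is also inflated. The schedule does not support this: HAMD, HbA1c, glucose and lipids have two assessments. They would be reached only if the general four-visit wording overrode Table 3.

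A reader might also take a two- to fivefold inflation as a property of this trial. The article gives no variances, the lower scenarios are near 1.4 times, and the upper ones need large true change with little noise. The interaction test is not named either; with visit as a factor it has 3 df and rejects in only about 5-10%.

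It may be said that residual covariance belongs in an analysis plan that is not shown. Degrees of freedom and convergence rules do. The random effect, however, is stated here, and lme4, one of the two listed tools, in ordinary use fits independent residuals, so following the text gives the equal-correlation model.

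Finally, this is a pilot sized for precision rather than testing. That lowers the stakes but does not remove them: the plan still applies a 0.05 rule, and precision is what a too-small standard error misstates. Nothing supports the further inference that the definitive trial would be planned wrongly, because the article does not say it will be sized on weight/BMI or on this model.

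**Conclusion.** The point holds conditionally. The article contradicts itself on whether two or four visits are analysed. If all four weight/BMI visits enter the random-intercept-only model and patients change at different rates or drift between visits, a single week-12 or slope test at nominal 5% rejects a true null in roughly 7-25% of trials, about 1.4 to 5 times nominal. A joint 3-df test rejects in about 5-10%. These figures rest on assumed variances, complete data and 30 per arm; with 26 per arm (about 13% dropout) they are nearly the same for the scenarios tried. Under exactly equal correlation, or with two assessments, the level is 5%. On Table 3 the reach is weight and BMI only. The change is worth making because it is cheap and concerns a primary outcome, but it does not touch the depression analysis as scheduled.

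**What to change.** In section 20a:

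1. State which visits enter the model for each outcome, and bring the opening sentence of 20a, the intervention section, the timeline text and Table 3 into agreement.
2. For any outcome with more than two visits (weight and BMI under Table 3), replace the random-intercept-only structure with visit as a categorical factor and an unstructured within-patient covariance. SPSS, already listed, can fit this with its MIXED procedure.
3. Name the week-12 between-group contrast as the test for those outcomes.
4. If that model does not converge, use ANCOVA of the week-12 value on the baseline value of the same outcome.
5. Keep the random-intercept model for outcomes with two assessments.

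With complete data and no covariates, the week-12 change contrast under an unstructured covariance is the two-sample comparison of change scores, which holds its level. The unstructured fit itself was not simulated. The week-12 ANCOVA was, and rejected in 0.046-0.052 of null trials.

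The cost is a few sentences and no extra data or patients. With four visits the covariance has 4 × 5/2 = 10 parameters instead of 2, which is feasible with about 60 patients, and the confidence interval for weight/BMI will be somewhat wider.
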